## Methods

### Study design and study area

This study will adopt a mixed-method research design. We will combine quantitative and qualitative approaches to obtain comprehensive results regarding the research questions [22]. The exploratory sequential mixed methods design will be conducted for the data collection. Data collection will be performed among patients who have been diagnosed with TB using chest X-ray and sputum smear microscopy. Four districts with the highest recorded cases in the state of Selangor will be selected as study locations. The sampling frame will be determined from the MyTB system database and patients fulfilling the inclusion criteria will be identified as sampling units. Thereafter, they will be categorised based on the four districts to ensure there are respondents from each district.

### Study population

The study population will comprise TB patients in the state of Selangor.

### Inclusion criteria

The following inclusion criteria will be used in recruiting the study participants:

Confirmed TB patients that were diagnosed using chest X-ray and sputum smear microscopy.TB patients from districts with the highest recorded cases in SelangorInformed consent to participate in the study

### Exclusion criteria

The exclusion criteria are as follows:

Suspected or unconfirmed TB patients.TB patients from districts with low recorded cases of TB in SelangorDecline to provide informed consent to participate in the study

### Sample size calculation and sampling technique

Sample size will be calculated using the formula for analytical and cohort studies [23, 24] as shown below:

$$n^{'}=\frac{{\left[z_{1-\alpha /2}\;\sqrt{2\overset{-}{P}\;\left(1-\overset{-}{P}\right)}+\;z_{1-\beta }\;\sqrt{P_{1}\left(1-P_{1}\right)+\;P_{2}\left(1-P_{2}\right)}\right]}^{2}}{({P_{1}-\;P_{2})}^{2}}$$

$$n=\frac{n'}{4}\;{\left(1+\;\sqrt{1+\;\frac{2\;(2)}{n^{'}\left(P_{2}-\;P_{1}\right)}}\;\right)}^{2}$$

Where,

n = Sample size

Z1 – α/2 = Z statistic for level of confidence of 95% = 1.96

Z1-β = Z statistic for 90% power = 1.28

P_1_ = Proportion with present condition in one group

P_2_ = Proportion with present condition in another group

P_1_ and P_2_ will be obtained from previous prevalence studies on patient and treatment delays among different groups of PTB patients. The obtained values will be substituted into the equation to compute the required sample size (n). Thereafter, the calculated sample size will be adjusted for eligibility by assuming that approximately 30% had delayed TB presentation [25]. Additionally, the sample size will be adjusted for the response rate.

Probability proportionate to size (PPS) technique will be used to allocate sample size for each district to enable proportionate allocation of patients from each healthcare facility in the district. A simple random sampling technique will be used to obtain the required number of patients from each district. A purposive sampling technique will be used for the selection of healthcare facilities in the district with a high prevalence of TB. Patients at each facility will be selected randomly using the MyTB database. Once the samples for the quantitative study have been identified, a subsample of respondents will be invited to join the qualitative study, with an equal number from each district.

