### Quantitative phase: Instrument development

A structured questionnaire will be constructed based on the themes identified in the qualitative study and a review of several studies in the literature. Operational definitions will be developed based on the themes obtained. The questionnaire will undergo content validity by three field experts. Then, it will be distributed to ten healthcare professionals for face validity assessment. Necessary modifications will be made based on the comments received. The final questionnaire will then be translated into the local language, Bahasa Malaysia, and pre-tested on 30 TB patients from selected hospitals and health clinics for the reliability or internal consistency. Based on the field experts’ opinions and pilot testing, potential ceiling and floor effects from the questionnaire items that may affect accurate data interpretation will be prevented.

For the quantitative phase, a cross-sectional study using the developed questionnaire will be distributed to the patients identified through the PPS technique at all selected hospitals and health clinics in all four districts. Finally, the data obtained from both qualitative and quantitative approaches will be combined to provide a more robust assessment of the study. The qualitative findings from the viewpoints of the participants in FGD will facilitate the interpretation of the study results, whereas the quantitative results will provide a better understanding of the study objectives and research questions [22]. An expert panel will be engaged to construct the social epidemiology framework model for delayed presentation of TB.

The research design in this study offers the strengths of both quantitative and qualitative approaches, thus providing a more robust outcome for this study. A mixed-method research design can also broaden the dimension and scope of the study [22]. Table 1 shows the research matrix and Fig 1 presents the overall research design of this study according to each research question.

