### Quality control measures

Several important methodological resources will be used to ensure quality data collection and minimise bias in the study. This includes the mixed-method study design, inclusion and exclusion criteria, random sampling technique and randomisation process. The principal researcher will collect all the data during the FGD, whereas additional enumerators will assist with the data collection during the quantitative phase. These enumerators will participate in distributing the questionnaire during the pilot test for them to get familiarised with the study instrument. Meanwhile, during the quantitative phase, the principal researcher will ensure that enumerators are following the survey protocol. Participants would be assisted while completing the questionnaire if necessary to minimise missing data. Another quality control measure is the principal researcher’s role by reviewing the completeness and quality of data in the returned questionnaires.

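### Purposive choice of facilities contradicts the claimed simple random sample of each district and can bias the district-level proportion delayed, in unknown direction and size

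*Protocol article*

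**What the plan says.** Under Study design and study area, the protocol article sets up a patient-level frame: "The sampling frame will be determined from the MyTB system database and patients fulfilling the inclusion criteria will be identified as sampling units". These patients are then grouped by the four districts.

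Sample size calculation and sampling technique gives four statements on how patients are reached:

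- Allocation: "Probability proportionate to size (PPS) technique will be used to allocate sample size for each district", with the aim of proportionate numbers from each facility in the district.
- Patients: "A simple random sampling technique will be used to obtain the required number of patients from each district".
- Facilities: "A purposive sampling technique will be used for the selection of healthcare facilities in the district with a high prevalence of TB".
- Within facilities: "Patients at each facility will be selected randomly using the MyTB database".

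Quantitative phase: Instrument development says the questionnaire will be "distributed to the patients identified through the PPS technique at all selected hospitals and health clinics in all four districts".

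Quality control measures, on minimising bias, says: "This includes the mixed-method study design, inclusion and exclusion criteria, random sampling technique and randomisation process".

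The article does not give the facility selection rule, the number of facilities, or the share of each district's cases that they hold.

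**The concern.** A simple random sample of a district gives every eligible patient in it the same chance of selection. Purposive choice of facilities removes that property at the first stage, and random drawing inside the chosen facilities cannot restore it. The two descriptions cannot both hold.

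This matters because the protocol itself links facilities to the outcome. The section on why the study is important names limited healthcare facilities among the reasons for late diagnosis. The Introduction lists provider-related barriers as a contributor to delay. Table 1 describes health-seeking behaviour as the time from symptom onset to first presentation at a facility, and makes the types of provider barrier an objective in their own right. Choosing facilities by judgement may therefore filter the sample on something the study sets out to measure. A larger sample does not reduce such an error.

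**Working it through.** **Step 1: which design operates.** Set side by side, the statements give:

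| Stage | Method stated | Probability sample? |
|---|---|---|
| Districts | Four with the highest recorded cases | Fixed by eligibility |
| Facilities | Purposive, rule unstated | No |
| Numbers per district and facility | Proportionate to size | Allocation only; draws no facility |
| Patients within facility | Random from MyTB | Yes |

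The survey goes only to selected hospitals and clinics, so this is a two-stage design with a non-probability first stage. An eligible patient at an unselected facility has inclusion probability 0. The sample is a random sample of a district only if the selected facilities hold all its eligible patients.

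**Step 2: size of the possible bias.** The plan states no figure to reproduce here. Let W be the share of a district's eligible patients at the selected facilities, and p_sel and p_un the proportions delayed at selected and unselected facilities.

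- District proportion = W × p_sel + (1 − W) × p_un
- Bias = p_sel − district proportion = (1 − W) × (p_sel − p_un)

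W and the difference are assumptions; the document gives neither. Absolute bias, in percentage points:

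| Coverage W | Difference 0 | Difference 5 | Difference 15 |
|---|---|---|---|
| 40% | 0 | 0.6 × 5 = 3 | 0.6 × 15 = 9 |
| 80% | 0 | 0.2 × 5 = 1 | 0.2 × 15 = 3 |
| 100% | 0 | 0 | 0 |

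The sign depends on whether delay is more or less common at the selected facilities, which is unknown.

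**Step 3: scale.** The article's planning figure is about 30% delayed. With an assumed n = 400, the simple-random-sampling 95% half-width is 1.96 × √(0.3 × 0.7 / 400) = 4.5 points. With an assumed n = 800 it is 3.2 points. Within the illustrative range the bias may be smaller or larger than sampling error.

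**Step 4: clustering (secondary).** Assume 20 patients per facility and an outcome intraclass correlation (ICC) of 0.02–0.05. For a factor that is constant within a facility:

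- Design effect = 1 + 19 × 0.02 = 1.38, up to 1 + 19 × 0.05 = 1.95
- True error of a nominal 5% test that ignores clustering = 2 × [1 − Φ(1.96/√design effect)] = 9.5% to 16%

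For a patient-level factor the design effect is about 1 + 19 × ICC_x × ICC_y. With ICC_y = 0.05 and an assumed ICC_x of 0.05–0.20 it is 1.05–1.19, and the true error is about 5.6–7.2%.

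**The case against.** The case on the other side has several sound parts.

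- **Facility criterion.** A reader might infer that facilities are picked for their own high prevalence, so that low-volume sites are the ones left out. The phrase can equally describe the district, which fits the eligibility criteria. The facility rule is then unstated, but selection remains purposive and the contradiction stands.
- **Bias as a shown result.** A reader might infer that the estimates will be biased by facility access. The document does not show this. It gives no coverage and no difference in delay between facilities, and it does not say that the facility used for sampling is where the patient first presented. Only the risk is established.
- **Regression coefficients.** A reader might conclude that no association carries over to the district. That needs more, such as effect modification by facility, or selection that depends on delay given the covariates. The document gives no ground for it.
- **Selangor.** Restriction to four districts is an explicit eligibility choice and is separate from how facilities are selected.
- **Independence.** Data analysis names multiple regression models and is silent on standard errors; it does not assert independence. That detail may sit in an analysis plan not shown, so it is no error here. The 9.5–16% figure applies to facility-level factors, not to every interval and p-value.
- **Existing safeguards.** Proportionate allocation with random drawing from MyTB makes the sample roughly self-weighting among the selected facilities. Listing random sampling as a control is therefore partly justified.

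What survives is the conflict between the sampling statements and the zero inclusion probability that follows from it.

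**Conclusion.** The point holds in a limited form. The sampling statements contradict each other. As the survey is described, patients at unselected facilities cannot enter, so the district random sample on which the quality-control section relies is not delivered. Nothing in the study is randomised beyond the sampling itself, so the reference to a randomisation process adds no protection.

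The consequence is a possible bias in the district-level proportion delayed and a possible narrowing of the provider barriers observed. The 1–9 point range is an illustration that rests wholly on assumed coverage and assumed differences. It is not an estimate.

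**What to change.** Before quantitative patients are drawn, replace the purposive step by one of these:

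- **(a)** A simple random sample from each district's MyTB list across all facilities. The frame already exists.
- **(b)** The same number of facilities as now intended, drawn at random within district with probability proportional to MyTB case count, followed by a fixed number of random patients per facility. With k facilities, m patients in each, M_i cases at facility i and M in the district, the inclusion probability is (k × M_i / M) × (m / M_i) = k × m / M, the same for every patient. Facilities so large that k × M_i / M exceeds 1 are taken with certainty and sampled at the district rate.

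If the facilities are already fixed, state the selection rule and the share of each district's MyTB cases they cover, and limit inference to those facilities.

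In every case, reconcile Study design and study area, Sample size calculation and sampling technique, Quantitative phase: Instrument development and Quality control measures, and delete the reference to a randomisation process. As a secondary, low-cost step, analyse with district strata and facility-clustered standard errors; this matters mainly for facility-level factors such as provider barriers.

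**Cost.** Possibly some different or additional sites, and slightly wider intervals. Focus-group participants were to be a subsample of the quantitative sample, and Timeline says they are already recruited, so their link to a redrawn sample must be checked. Option (b) and the restricted-inference route need no extra patients or staff.

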**Fig 1 pone.0266746.g001:**
[figure not shown]
Research design of the different study phases.

**Table 1 pone.0266746.t001:** Research matrix.

RESEARCH OBJECTIVES	QUANTITATIVE	QUALITATIVE
To describe the incidence of TB in Selangor and the health-seeking behaviour (timeline between the onset of symptoms to the first presentation to the healthcare facility and medical visit) among the patients.	√	√
To describe the social epidemiological characteristics (socio-demographic and socio-cultural) of the TB patients in Selangor.	√	
To determine the types of health provider barriers that are prevalent in Selangor.	√	√
To determine the association between health-seeking behaviour and social epidemiological factors (socio-demographics and socio-cultural) as well as health provider barriers.	√	
To investigate the key factors that contribute to delayed presentation of TB patients.		√
To construct a predictive social epidemiology framework for the identification of delay in seeking treatment among TB patients in Selangor.	√	√

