### Data analysis

For the qualitative phase, interview transcripts will be analysed using NVivo (Version 12). The software will be used to develop the main themes and sub-themes from the focus group discussion. Meanwhile, the quantitative data will be analysed using the IBM SPSS for Windows (version 25.0, Armonk, NY. IBM. Corp.). Cronbach alpha values will be computed from the reliability test to assess the reliability and to ensure the internal consistency of the questionnaire items. Cronbach alpha values of more than 0.7 will be accepted as reliable. Descriptive statistics will be used to summarise the data regarding participants’ socio-demographic characteristics, socio-cultural factors, health-seeking behaviours, and delayed presentation of TB.

The independent variable in this study is the delayed presentation of TB (measured in time: days and weeks), hence, the data will be subjected to normality tests using the level of kurtosis and skewness. Means and standard deviations will be presented for normally distributed data, whereas if the assumption of normality is not met, median and interquartile range will be presented. The cumulative incidence of TB will be estimated based on the number of new cases of TB divided by the total number of participants at risk. Determinants of delayed TB presentation will be analysed using multiple regression models. All parameter estimates will be computed at a 95% confidence interval, and statistical significance will be reported at *p* < 0.05. Lastly, a measurement model and structural modelling analysis will be performed using SmartPLS 3.0.

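### The sample size assumes independent patients while patients appear to be drawn within chosen facilities; for factors that cluster by facility, the 90% power is then overstated and a regression ignoring facility would be too precise

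*Protocol article*

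**What the plan says.** All references are to the Methods of the protocol article.

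- **Sizing.** Sample size calculation and sampling technique prints a two-proportion formula with a continuity correction. Its constants are "Z statistic for level of confidence of 95% = 1.96" and "Z statistic for 90% power = 1.28". The two proportions "will be obtained from previous prevalence studies on patient and treatment delays among different groups of PTB patients".
- **Adjustments.** Two are listed. First, "the calculated sample size will be adjusted for eligibility by assuming that approximately 30% had delayed TB presentation"; second, an adjustment for response rate, with no rate given. No design effect or ICC appears.
- **Sampling.** The same section chooses healthcare facilities purposively and then says: "Patients at each facility will be selected randomly using the MyTB database". Quantitative phase: Instrument development has the questionnaire "distributed to the patients identified through the PPS technique at all selected hospitals and health clinics in all four districts". However, the sampling section also says that each district's quota of patients comes from simple random sampling, which is a different design.
- **Analysis.** Data analysis says: "Determinants of delayed TB presentation will be analysed using multiple regression models". It adds 95% confidence intervals and a 0.05 significance threshold, and is silent on facility.
- **Exposures.** One objective in Table 1 is: "To determine the association between health-seeking behaviour and social epidemiological factors (socio-demographics and socio-cultural) as well as health provider barriers".

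**The concern.** The formula counts every patient as a separate piece of information. If several patients come from the same hospital or clinic, their delays may be correlated through shared catchment, access or providers. For an exposure that is the same for everyone at a facility, the information then depends largely on the number of facilities. Provider barriers are the listed exposure most likely to behave this way, although the article does not say at what level they are measured.

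Two things are at stake. The 90% power would not apply to such factors at the formula's n. And if the regression ignored facility, ordinary differences between facilities could pass the 0.05 threshold and be reported as determinants of delay. Both would hold even if the facilities were drawn at random, so this is separate from the purposive choice.

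**Working it through.** **1. The plan's own figures.** Φ(1.28) = 0.8997, so 1.28 matches 90% power, and 1.96 matches a two-sided 5% level. The formula is the standard continuity-corrected one for two equal independent groups, with n per group. No planned n can be reproduced, because neither proportion, the response rate nor N is stated.

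**2. Inputs for clustering (assumed).** The article gives no ICC, number of facilities or patients per facility (m). I take ICC 0.01 to 0.05 and m of 10 to 30.

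**3. Formulas, for a factor constant within facility.**
- Design effect: DEFF = 1 + (m − 1) × ICC
- Power at the formula's n before continuity correction: Φ(3.24/√DEFF − 1.96), where 3.24 = 1.96 + 1.28
- Type I error of a 5% test that ignores facility: 2 × [1 − Φ(1.96/√DEFF)]

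Example with m = 20, ICC = 0.02: DEFF = 1 + 19 × 0.02 = 1.38. Power = Φ(3.24/1.175 − 1.96) = Φ(0.80) = 0.788. Error = 2 × [1 − Φ(1.67)] = 0.095.

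| ICC | m | DEFF | Power | Type I error if facility is ignored |
|---|---|---|---|---|
| 0.01 | 10 | 1.09 | 87% | 6% |
| 0.02 | 10 | 1.18 | 85% | 7% |
| 0.02 | 20 | 1.38 | 79% | 9.5% |
| 0.02 | 30 | 1.58 | 73% | 12% |
| 0.05 | 10 | 1.45 | 77% | 10% |
| 0.05 | 20 | 1.95 | 64% | 16% |
| 0.05 | 30 | 2.45 | 54% | 21% |

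The power column hardly depends on the two proportions: the pairs 0.30/0.40, 0.30/0.45, 0.30/0.50 and 0.25/0.35 gave nearly the same percentages.

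**4. Scale in patients (illustration).** With assumed proportions 0.30 and 0.40, the formula gives 476 per group before and 496 after continuity correction. Multiplying the unrounded 495.4 by 1.38 gives 684 per group, and by 1.95 gives 966.

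**5. Factors that are not constant within facility.** For a factor whose own ICC is 0.2, DEFF = 1 + (m − 1) × ICC × 0.2. With m = 20 this is 1.076 at ICC 0.02 and 1.19 at ICC 0.05, so power is about 88% and 84%. For a factor balanced within facilities and adjusted for facility, power stays at about 90% to 93%.

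**6. The 30% adjustment.** If it means dividing by 0.30, which the text does not make clear, the sample grows by 1/0.30 = 3.33. Take ICC 0.05 and m = 20 at the formula's n:
- If facilities are added so that m stays 20, the effective sample is 3.33/1.95 = 1.71 times the formula's n, and power is Φ(3.24 × √1.71 − 1.96) = 99%. The type I error if facility is ignored remains 16%.
- If the number of facilities is fixed, m becomes 66.7 and DEFF = 1 + 65.7 × 0.05 = 4.28. The effective sample is 3.33/4.28 = 0.78 times the formula's n, power is Φ(3.24 × √0.78 − 1.96) = 82%, and the error is 2 × [1 − Φ(1.96/√4.28)] = 34%.

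This adjustment could therefore restore the power, but it cannot cure the error of a model that ignores facility.

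**The case against.** Several counter-arguments have force.

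- **The regression may already handle facility.** A reader might infer that the plan treats patients as independent in the regression. The article does not say so. It names multiple regression only, and a journal article can leave random effects or robust errors to a fuller plan. This stands: the statement about intervals is conditional on a model that ignores facility.
- **The sample may not be clustered.** Simple random sampling of patients across a district would remove most of the problem. This also stands as a possibility. But it does not fit with purposively chosen facilities and selection within each, and the section on the quantitative phase follows the facility route.
- **The 90% was set for comparing patient groups.** A reader might infer that it is overstated throughout. It is not: step 5 shows little or no loss for factors that vary within facilities.
- **Provider barriers may be reported by patients.** The only quantitative instrument described is a patient questionnaire, so answers could vary within a facility. The article does not settle this. Also, the delay before first presentation precedes care, and the sampled facility need not be where the patient first presented. Shared catchment is therefore a more plausible source of correlation than shared providers.
- **The eligibility adjustment may enlarge the sample.** It may, as step 6 shows, with the limits given there.
- **The framework rests on more than regression p-values.** An expert panel constructs it, and a structural model in SmartPLS is also planned. It would go too far to say that a false determinant enters the framework automatically. Changing the regression also does not alter the SmartPLS model.

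What the objections leave untouched is the mismatch within the sizing section: a formula for independent patients and a listed set of adjustments without a design effect, beside selection of patients within facilities.

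**Conclusion.** The concern holds in conditional form. If sampling is by facility, the 90% power at the formula's n is overstated for factors that are constant or strongly clustered within facility, and a regression that ignored facility would give intervals that are too narrow for those same factors. With 20 patients per facility, the illustration is about 79% power and 9.5% type I error at an ICC of 0.02, and about 64% and 16% at 0.05. At an ICC of 0.01 with 10 patients per facility, the effect is minor (87% and 6%).

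These figures rest on assumed ICCs and facility sizes. The actual loss cannot be determined, since N, both proportions, the ICC, the number of facilities and patients per facility are unstated, and the effect of the 30% adjustment on the final n is unclear.

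**What to change.** 1. **Reconcile the sampling description.** In Sample size calculation and sampling technique, state whether patients are drawn by simple random sampling across a district or within each purposively chosen facility. If the former truly applies, most of this point falls away.
2. **If sampling is by facility, state the regression accordingly.** In Data analysis, specify a facility random intercept or facility-clustered standard errors, with a small-sample correction if facilities are few, and district (the allocation stratum) as a fixed effect.
3. **Restate the power.** Say that 90% holds for independent patients. For facility-clustered factors, report power after dividing n by 1 + (m − 1) × ICC, for the chosen m and an ICC range such as 0.01 to 0.05. State what the 30% adjustment does to n, so that the power refers to the sample actually surveyed.

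The cost is some wording and a few lines of analysis code. Facility should be known from the MyTB sampling frame, and SPSS 25 has mixed-model and GEE procedures. The downside is somewhat wider intervals for facility-clustered factors and a less favourable stated power. No added patients are required; restating the power does not raise it, but it shows which comparisons the study can support.
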